**Figure 1 fig1:**
[figure not shown]
ScreenEQUAL Stage 1 overview.

**Figure 2 fig2:**
[figure not shown]
ScreenEQUAL Stage 2 overview.

**Figure 3 fig3:**
[figure not shown]
ScreenEQUAL study timeline.

## Methods and analysis

2

### Inclusive study methods

2.1

#### ScreenEQUAL co-production study framework

2.1.1

The study will adhere to the principles of the inclusive research framework “Doing Research Inclusively: Guidelines for Co-Producing Research with People with Disability” (36), and an integrated knowledge translation (iKT) model of research co-production, whereby researchers’ partner with knowledge users throughout the research process to support translation of research findings into practice and policy (37).

It will also adopt a trauma-informed approach to minimise the risk of re-trauma of participants with intellectual disability due to the sensitive nature of cervical screening and the potential impact of a history of sexual assault or previous negative screening experiences (38). Trauma-informed practice is grounded in the understanding that trauma exposure can impact an individual’s neurological, biological, psychological and social development (38, 39), and seeks to address the barriers that people affected by trauma can experience when accessing health and care services.

A ScreenEQUAL Advisory Group will be convened, including people with intellectual disability and other stakeholders from the disability, cancer, and healthcare sectors, with representation across regional and rural, Aboriginal and Torres Strait Islander, culturally and linguistically diverse (CALD) and LGBTQ+ communities. Its governance structure will foreground members with intellectual disability representing grassroot community-based organisations. Two Advisory Group meetings will be held annually, with individual pre, and post meeting preparation and debriefing for members with intellectual disability, to optimise participation and mitigate risks of re-traumatisation. Grassroot organisations run by and for people with intellectual disability, who will be represented on Advisory Group, will be compensated for their time in line with community standards.

Each research team member will undertake Easy Read training which will be universally used to ensure accessibility of study documents and communications (40). Stages 1 and 2 will include optional body-mapping, an arts-based participatory research method, for participants with intellectual disability, to align with participants’ preferences. Body-mapping involves the participant (or, if preferred, an expert disability researcher) tracing around their body to create a life-sized outline and being invited to fill their body outline by drawing or attaching pictures, writing words, or using colours, associated with their own experiences with cervical screening (41) (a de-identified example from the preparatory phase of the study is shown in Figure 4).

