#### Recruitment and gaining informed consent for participants with intellectual disability

2.1.3

The research team will collaborate with disability services and community-based advocacy organisations including those with which the research term has existing professional relationships to identify potentially eligible participants for study Stages 1 and 2. These include at least three grassroot self-advocacy organisations run by and for people with intellectual disability, and a large national private disability service supporting people with intellectual disability. The research team will also give presentations about the study at community disability forums to establish new connections with a diverse range of services and grassroot organisations.

The research team will consult the Advisory Group throughout the study to identify new sources of recruitment for potential participants with intellectual disability with diverse needs and backgrounds. This may include, if appropriate and where trusted relationships have been established, closed social media groups for people with intellectual disability, their families and support people as well as smaller grassroot community organisations and disability services.

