#### Main trial participants – people with intellectual disability

2.4.1

People with intellectual disability will be eligible for participation in the single-arm main trial if they are due or overdue for cervical screening in the NCSP (age 25 to 74 years with a cervix) and can communicate verbally or non-verbally including through augmentative and alternative communication (Figure 2). Participation in Stage 1 will preclude participation in Stage 2 to reduce the chance of trial participants having enhanced knowledge of cervical screening prior to the intervention (Table 3). A separate consent process will seek permission for the research team to access participants’ cervical screening histories from the Cancer Institute NSW Cancer Screening Register at a 9-month timepoint after the trial. Participants who do not consent to their screening history being accessed, will not be excluded from the trial. Participant recruitment and processes for gaining informed consent are outlined in Section 2.1.3.

**Table 3 tab3:** Eligibility criteria for Stage 2 main trial and single-arm sub-study participants.

Participant group	Eligibility criteria
People with intellectual disability	Person with intellectual disability; due or overdue for cervical screening in the NCSP (age 25 to 74 years with a cervix); can communicate verbally or non-verbally (including through augmentative and alternative communication); has not participated in Stage 1 of the study
Family members and support people	Family member or support person (unpaid or paid, for example, disability support worker) of a person/people with intellectual disability who are eligible for screening in the NCSP; live or work in Australia; speak English.
Healthcare providers	GP or nurse who works with people with intellectual disability who are eligible for screening in the NCSP; practice in Australia; speak English.

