#### Main trial design

2.4.2

The main trial is a single-arm study aimed at evaluating the primary study outcome (a change in informed decision-making about cervical screening by people with intellectual disability). An accessible informed decision-making tool will be created based on existing tools and surveys informed by the research team, Advisory Group members with intellectual disability and experts in health literacy. The modified tool will collect data via interviews using a brief set of pre-intervention open-ended accessible questions across three domains: knowledge, attitudes to screening and intention to screen (49–52). The trial will serve as a pilot study for a larger appropriately powered validation trial.

People with intellectual disability (*n* = 48) will be invited to join one of 5 or 6 accessible workshops of approximately 10 people with intellectual disability and 2 to 3 trained support people, facilitated by members of the research team. The workshops will last approximately 2 to 3 h. Support people will be identified through Family Planning Australia networks to participate in a pre-workshop session where they will receive training according to a structured session plan on how to use the co-produced resource with people with intellectual disability. The trained support people will then use the resource with workshop participants in a way that simulates what would happen in a community setting (the intervention). Individual participants with intellectual disability will be supported to complete a brief set of pre-intervention open-ended accessible questions to assess informed decision making at the start of the workshop which will be repeated at the end of the workshop or within the next week depending on the participant’s choice. Qualitative data regarding the overall perceptions of the co-produced resource will be gathered during the workshops by the research team through audio-recording of the group discussion.

A subset of participants with intellectual disability (*n* ≈ 20 or until saturation is reached) will be invited to participate in post-intervention qualitative interviews, with the option of additional body-mapping, to provide further insights into perceptions of the resources and to support the interpretation of the study outcomes (41).

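### The main trial's prior-knowledge exclusion covers Stage 1 participants but not the Advisory Group members with intellectual disability who inform the primary-outcome tool

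*Protocol article*

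**What the plan says.** Section 2.4.1 gives a rule and its reason: "Participation in Stage 1 will preclude participation in Stage 2 to reduce the chance of trial participants having enhanced knowledge of cervical screening" before the intervention. Table 3 carries the rule as one criterion, "has not participated in Stage 1 of the study". The other conditions there are having an intellectual disability, being able to communicate verbally or non-verbally, and being "due or overdue for cervical screening in the NCSP (age 25 to 74 years with a cervix").

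Section 2.1.1 sets up the Advisory Group, stating that "A ScreenEQUAL Advisory Group will be convened, including people with intellectual disability". It meets twice a year, with individual preparation and debriefing for members with intellectual disability, and those members represent grassroot community organisations. Section 2.4.2 says the informed decision-making tool will be "informed by the research team, Advisory Group members with intellectual disability and experts in health literacy". Section 2.5.1 makes that tool the measure of the primary outcome.

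On recruitment, section 2.1.3 names "at least three grassroot self-advocacy organisations run by and for people with intellectual disability" as a source, adds snowballing among friends, and says "The research team will consult the Advisory Group throughout the study to identify new sources of recruitment".

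Section 2.3 and Table 1 describe Stage 1 participants as people who are interviewed or attend co-production workshops. Advisory Group membership is not described as Stage 1 participation.

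**The concern.** The criterion is narrower than its own purpose. A Stage 1 participant with intellectual disability, whose interview lasts about an hour, is excluded because of what they may have learned. An Advisory Group member with intellectual disability, who has contact with the study over its course and informs the questions that decide the primary outcome, is not.

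The main trial has no control arm, so the primary result is the pre-post change alone. A person already classed as informed at the first measurement cannot improve. Each such person raises the baseline and reduces the observable change. The Discussion treats even indirect prior awareness, through networks shared with Stage 1 participants, as a limitation. It does not mention this more direct route.

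**Working it through.** **1. Who is excluded.**

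| Group | Exposure described | Excluded from the main trial? |
|---|---|---|
| Stage 1 interviewees and workshop attendees | Interview of about an hour, or workshops of about 4 hours | Yes (2.4.1, Table 3) |
| Advisory Group members with intellectual disability | Two meetings a year, input to the website (2.3.4), informing the primary-outcome tool (2.4.2) | No statement |

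**2. The plan's own sample size.** Section 2.4.3 gives 20% before and 50% after (difference 0.30), standard deviation 0.5 at each time, zero correlation, 80% power and alpha 5%. Section 2.5.2 makes tests two-sided.

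- SD of the difference = √(0.5² + 0.5²) = 0.7071
- n = ((1.96 + 0.8416) × 0.7071 / 0.30)² = 43.6, so 44. The stated figure is reproduced.

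**3. Effect of k people already informed.** The article does not give the number of Advisory Group members, so k is an assumption. I take the worst case for dilution: each of the k is informed at both times, and the other 44 − k follow 20% to 50%.

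- Baseline = 0.20 + 0.80 × k/44
- Expected change d = 0.30 × (1 − k/44)

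*Variance A, the plan's SD of 0.5 throughout:* SE = √(0.5/44) = 0.1066; power = Φ(d/SE − 1.96).

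*Variance B, implied by 20% and 50% with independent measurements:* for the 44 − k, the variance of the difference is 0.2×0.8 + 0.5×0.5 = 0.41, so its mean square is 0.41 + 0.09 = 0.50. The k people contribute zero change. Overall variance = 0.50 × (1 − k/44) − d²; SE = √(variance/44); power as above.

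| k of 44 | Baseline | Expected change | Power, A | Power, B |
|---|---|---|---|---|
| 0 | 20.0% | 30.0 points | 0.804 | 0.8745 |
| 1 | 21.8% | 29.3 points | 0.785 | 0.865 |
| 2 | 23.6% | 28.6 points | 0.766 | 0.856 |

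From k = 0 to k = 1 or 2, power falls by about 2 or 4 points under A and about 1 or 2 points under B. Variance A overstates the loss, because it keeps full variability for people assumed not to change at all.

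**The case against.** The best reply is that this is a gap in wording, not a plan to enrol advisers. The article presents them as governance and as a guide to finding participants. To enter, an adviser would have to be 25 to 74, have a cervix, be due or overdue for screening, and be recruited in New South Wales (section 2.2). The group also feeds into work described under Stage 1, namely the interview guides and the website, so one could read its members as having taken part in Stage 1. The bias runs toward no effect, so it could not create a false claim of benefit, and the trial is described as a pilot for a larger validation trial.

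Most of this stands, and it limits the size of the point. It does not close the gap. The article states both the criterion and its reason, and the reading that counts advisers as Stage 1 participants is nowhere explicit.

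Three stronger readings are tempting but not supported:

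- *That preparatory-phase participants are a second missed group.* The article says only that "a de-identified example from the preparatory phase of the study is shown in Figure 4". It does not say who made the body-map, how many people took part, what they learned, or whether that phase counts as Stage 1. Section 2.3.2.1 invites team members to body-map too.
- *That advisers write or check the questions.* Section 2.4.2 says only that they inform the tool.
- *That power falls materially.* With k = 6, variance A gives about 68%. But six people would be 14% of the 44, no such number appears in the article, and variance B gives about 81% for the same k.

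**Conclusion.** The exclusion falls short of its stated purpose for one identifiable group, Advisory Group members with intellectual disability, and it should be widened. The consequence is a possible rise in the baseline and a shift of the pre-post change toward zero. For one or two such people among 44, the expected change falls from 30 points to about 29, and power falls by roughly 1 to 4 points depending on the variance used. These figures assume that such people enrol and that they are informed at both measurements; the article establishes neither. A reader might infer that the sample size is wrong or that the trial is likely to be underpowered for this reason. Neither follows: 44 is reproduced from the plan's own inputs, and both 44 and 48 stand.

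**What to change.** In Table 3 (people with intellectual disability) and in section 2.4.1, extend the criterion to read along these lines: *has not participated in Stage 1, the ScreenEQUAL Advisory Group, or the development or piloting of the informed decision-making tool*. Check it at consent. Separately, state in one sentence whether the preparatory phase counts as Stage 1.

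The cost is one clause and a few people becoming ineligible. The Ethics statement says Stage 2 ethics approval and registration are still to come, so the change can be made before either. The sample size needs no revision.

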**Figure 4 fig4:**
[figure not shown]
A de-identified body-map from the preparatory study phase.

To foreground perspectives of people with intellectual disability in data analysis and interpretation, we will use creative, accessible, and participatory processes such as visual representations of the data, participatory videos, role-playing and/or co-analysis workshops, guided by the Disability Inclusive Guidelines (36) and recommendations from the study Advisory Group.

#### Supporting a culturally safe trial design

2.1.2

The study was originally conceived as a cluster randomised control trial (cRCT) with clusters comprised of single healthcare providers and multiples of people with intellectual disability for whom they provide services, their family members and/or support people. However, a decision to shift to a pragmatic single-arm trial design for people with intellectual disability and sub-studies for independent groups of family members and support people, and healthcare providers, was made at the study planning stage. This shift was to ensure feasibility and an ethically sound approach after significant study design challenges became evident during community consultations. The extent of overall negative healthcare experiences exposed by the Royal Commission into Violence, Abuse, Neglect and Exploitation of People with Disability (21) published at the time of planning, helped inform the decision to use a single-arm trial design rather than clustering participants with intellectual disability together with their healthcare provider, family member and/or support worker, as was proposed in the original design. Other challenges with the initial design included the potential for distress for those allocated to a control group, the practicalities of recruiting sufficient participants with intellectual disability to meet the RCT sample size requirements (*n* = 200), and recognition that high rates of sexual assault amongst this population would necessitate additional supports beyond the research team’s capacity.

#### Recruitment and gaining informed consent for participants with intellectual disability

2.1.3

The research team will collaborate with disability services and community-based advocacy organisations including those with which the research term has existing professional relationships to identify potentially eligible participants for study Stages 1 and 2. These include at least three grassroot self-advocacy organisations run by and for people with intellectual disability, and a large national private disability service supporting people with intellectual disability. The research team will also give presentations about the study at community disability forums to establish new connections with a diverse range of services and grassroot organisations.

The research team will consult the Advisory Group throughout the study to identify new sources of recruitment for potential participants with intellectual disability with diverse needs and backgrounds. This may include, if appropriate and where trusted relationships have been established, closed social media groups for people with intellectual disability, their families and support people as well as smaller grassroot community organisations and disability services.

A member of the research team known to the disability organisation or service will be responsible for sending a letter of invitation requesting support for the study. Those interested will be invited to introduce the project to potentially eligible participants using a range of tailored approaches. Grassroot self-advocacy organisations will be invited to share an Easy Read participant information statement and study consent form (PISCF) with potentially eligible participants by advertising the study through their accessible websites and/or newsletters. Private disability services providing supported or independent living accommodation will be invited to share information about the study via their website and/or online newsletters, and to provide copies of the Easy Read PISCF to relevant site managers, who can in turn provide in-person information and the PISCF to eligible clients. The PISCF also includes links to an accessible information video (Figure 5) (40). This approach aims to make the study aims easily understood and to facilitate voluntary informed consent by participants. Potential participants can indicate their interest by contacting the researchers directly by telephone and/or email. Recruitment will also be supported by posting Easy Read social media advertisements (e.g., X – formerly Twitter, LinkedIn, Facebook) (Figure 6), and ‘snowballing’ whereby people with intellectual disability recommend participation to their friends, which is more likely if they have had a positive experience with the study.

**Figure 5 fig5:**
[figure not shown]
Screenshots of the of the accessible information video.

**Figure 6 fig6:**
[figure not shown]
Screenshot of the easy read social media advertisement.

The initial consent processes for study participation and all qualitative interviews (including participation in workshops) with participants with intellectual disability will be conducted by the expert disability researchers in the field of applied research in intellectual disability, including the chief investigator with intellectual disability. Mitigation strategies will be in place for participants who show signs of distress. This may include cessation of an interview, and follow-up with the participant and their support person to check whether additional support is needed through referral to a regular general practitioner (GP) or an appropriate counselling service. Participants in other groups who experience distress will also be provided with support through appropriate services, if required.

During the consent process, participants will have the opportunity to meet the interviewers at a location of their choice and ask any questions, prior to their interview. This process is important in enabling participants to develop rapport with the researchers conducting the interview, before deciding whether to take part in the study. The interviewers will explain the study in an accessible way using the Easy Read PISCF. The chief investigators conducting the interviews with people with intellectual disability are experienced in using alternative methods of communication, such as augmentative and alternative communication (e.g., pictograms, electronic speech generating devices) or arts-based methods (e.g., photographs, body-mapping) to engage potential participants with high support needs, including those with complex communication needs (42). A continuous (written and verbal) consent process will be used before, during, and after data collection. This will include checking with the participant that they continue to consent to their data being collected and analysed after their participatory interview, or whether they would like to withdraw from the study without penalty. Accessible information about the study, and the co-produced cervical screening information resource, supporting materials and training materials will be available on a co-produced ScreenEQUAL website.

### Study setting

2.2

Participants with intellectual disability will be recruited from metropolitan, regional and rural areas of New South Wales, Australia, due to the necessity of in-person contact with the research team. Participants in the other groups (families, support people, healthcare providers and disability sector stakeholders) will be recruited from across Australia.

### Stage 1 methods and analysis

2.3

Semi-structured interviews will be conducted to explore facilitators and barriers to cervical screening experienced by people with intellectual disability. A series of workshops will then be held to co-produce a suite of resources and materials to support cervical screening informed decision-making by people with intellectual disability (Figure 1).

